#### Inclusion criteria

In order to be eligible to participate in this study patients must have received prescriptions for antidepressants in primary care for at least the past 9 months and be 18 years or older.

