### Randomization and statistical analysis

To prevent a crossover effect between the interventions, cluster-randomization will be performed with the GP as the unit of clustering. A senior academic statistician will produce the randomization schedule based on a stratified block randomization. Stratification variables consist of region (north, central and east Netherlands) and type of practice (single versus group practice). This schedule will be send in a protected Excel-sheet to a research assistant who will allocate the GP in order of their entry to either intervention or control group. The research assistant will communicate the allocation to the researcher who will, in turn, communicate this to the GP. We are not able to keep the SCID interviewer blind to the patient’s condition. The clinical outcome data will be analysed and reported according to the CONSORT guidelines, i.e. both on an intention-to-treat and per protocol basis. With regard to missing data, sensitivity analyses will be conducted with different types of imputation. Multilevel analyses will be used to account for the hierarchical structure of the data (i.e. multiple assessments nested within patients, patients nested within GPs, and GPs nested within practices).

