### Primary analysis

The primary analysis is aimed at comparing the effects of SPD and SPD + MBCT with regard to the proportion of patients who fully discontinue their antidepressant medication within 6 months. Full discontinuation is defined as using 0 mg antidepressant medication before or at the 6-month assessment. Patients who drop out before this assessment will be classified as ‘not able to discontinue’ (for the primary outcome variable). However sensitivity analyses will be conducted to examine different types of imputation. We will use a multilevel logistic regression model for repeated measures to analyze differences between the two conditions on baseline, 6 months, 9 months and 12 months follow-up measurements.

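### The primary outcome is a single 6-month proportion, but the only model stated is a four-occasion repeated-measures logistic regression that includes an all-zero baseline and names no primary contrast

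*Protocol article*

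**What the plan says.** The Primary analysis section says the comparison is made "with regard to the proportion of patients who fully discontinue their antidepressant medication within 6 months". It then fixes the variable: "Full discontinuation is defined as using 0 mg antidepressant medication before or at the 6-month assessment". Early dropout is settled too ("Patients who drop out before this assessment will be classified as" not having managed to discontinue), so each patient has one complete yes/no result at 6 months.

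The same section ends with its only model, a "multilevel logistic regression model for repeated measures to analyze differences between the two conditions on baseline, 6 months, 9 months and 12 months" follow-up. It does not say how time is coded, which variable is analysed at 9 and 12 months, or which term carries the primary test. The section on randomization and statistical analysis adds the hierarchy: assessments within patients, patients within GPs, GPs within practices. A patient-level random effect is therefore part of the plan.

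On the state at baseline, the Inclusion criteria require that patients "must have received prescriptions for antidepressants in primary care for at least the past 9 months". The Procedure section places the supported-discontinuation meetings after the baseline measures.

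**The concern.** The hypothesis, the outcome definition and the sample size all concern one comparison of two proportions at 6 months. The model concerns four occasions, and on one of them the outcome cannot vary. A logistic model has no finite estimate for a cell with no events, so baseline can serve neither as a reference visit nor as an informative comparison.

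The choices left open decide whether the primary result is valid, distorted or meaningless: how time is coded, whether later visits use current status or a cumulative outcome, and which contrast is tested. The Design section says that the research team knows the allocation. If the model has to be replaced after it misbehaves, that choice would be made by people who can see which version favours which arm.

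**Working it through.** **1. The plan's own sample size.** Inputs from the Sample size section: 15% versus 40%, two-sided alpha 5%, power 80%, ICC 0.05, 5 patients per GP, 15% dropout.

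- Two proportions, pooled variance, no continuity correction: n = [1.960·√(2·0.275·0.725) + 0.842·√(0.15·0.85 + 0.40·0.60)]² / 0.25² = 48.9, so 49 per arm.
- Design effect: 1 + (5 − 1)·0.05 = 1.2, and 49·1.2 = 58.8.
- Dropout: 58.8/0.85 = 69.2 per arm, 138.4 in total, against 138 stated.

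The figure is reproduced. It rests on one comparison of two 6-month proportions, with OR = (0.40/0.60)/(0.15/0.85) = 3.78, log OR 1.33.

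**2. Stated model on expected counts.** 69 per arm; 0/69 in both arms at baseline; 10/69 versus 28/69 (14.5% versus 40.6%) at 6, 9 and 12 months. That the rates stay flat after month 6 is an assumption. Ordinary logistic fits, no random effects:

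| Coding | 6-month arm effect | Result |
|---|---|---|
| 6-month data only | log OR 1.39, SE 0.42 | p = 0.0009 |
| Categorical time, baseline as reference, arm-by-6-month interaction | 1.39, SE 36,774 | z about 0 |
| Same fit, explicit contrast (arm + arm × 6 months) | 1.39, SE 0.42 | p = 0.0009 |
| Linear time | fitted 8.4% versus 24.4% | actual 14.5% versus 40.6% |

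Check of row 1: ln[(28/41)/(10/59)] = 1.39; SE = √(1/28 + 1/41 + 1/10 + 1/59) = 0.42.

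In row 2 the intercept has run to −25.6 with SE 26,003. The exact size of such standard errors only reflects where the iterations stopped; the true estimate is infinite. In row 4 the fitted risk difference is 24.4 − 8.4 = 16.0 points, against 40.6 − 14.5 = 26.1.

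**3. Adding the patient random intercept, current status at each visit.** One simulated data set, 69 per arm, 6-month rates 10.1% and 39.1%. With visit-specific arm terms, the 6-month log OR is 2.95 with baseline and 2.95 without, and the log-likelihood is −200.493 both ways. Only the baseline terms diverge. The crude 6-month log OR is 1.74. As odds ratios, that is exp(2.95) = 19.1 against exp(1.74) = 5.7. Three further simulated data sets gave 1.74, 3.79 and 1.77, the same with and without baseline, against crude values of 0.97, 1.72 and 1.08.

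**4. If the definition were carried forward.** Suppose discontinued at or before each visit were the outcome at 9 and 12 months as well, so that a success could never revert. In four simulated data sets (5% further accrual per later visit assumed), the random-intercept fit failed in all four: random-intercept SD 74 to 90, 6-month log OR 32 to 107, against crude values of 0.9 to 2.0. Dropping baseline did not rescue it, so this failure comes from the cumulative outcome and not from the baseline visit.

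**The case against.** The strongest reply is that the model works if read sensibly. Six months is one of the listed visits, differences at each listed time read naturally as visit-specific comparisons, and the section opens by naming the 6-month proportion. Under that reading baseline is idle and does no harm, as steps 2 and 3 show. That stands. A reader might infer that the whole model cannot be estimated, or that it does not test the 6-month proportion at all; the document supports neither. It leaves the test undefined rather than excluding it.

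The breakdown in step 4 must also be kept in its place. The cumulative definition is given only for 6 months. The Safety and monitoring section lets patients restart at any time, and restarting is among the secondary hypotheses, so status at later visits can revert. Step 4 shows what one unstated choice would do, not what the plan prescribes.

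A patient-specific odds ratio above the crude one is not an error in itself. In comparison runs the test statistic was much the same as from 6-month data alone (z 2.74 versus 2.79, 3.81 versus 3.84, 1.90 versus 1.99). What differs is the scale of the reported effect.

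One might add that the model omits the stratification factors ("Stratification variables consist of region (north, central and east Netherlands) and type of practice (single versus group practice"). Covariate lists are ordinary analysis-plan detail, so their absence from an article is no finding. An unseen analysis plan might likewise name the contrast. That does not dispose of the point: the article is not silent here, but states a model that does not match its outcome and lists baseline as an outcome occasion. The rule in the Secondary analyses section on baseline covariates does not help, since it covers continuous variables.

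**Conclusion.** The point holds in this form: the stated model is mismatched to the single 6-month proportion that defines and sizes the trial, its primary contrast is not fixed, and baseline does not belong among the outcome occasions. The consequence depends on the reading:

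- With a baseline-referenced interaction, the 6-month effect has no usable test.
- With linear time, the 6-month risk difference shrinks from 26.1 to 16.0 points on the expected counts.
- With visit-specific terms and current status, the test is essentially sound, but the odds ratio is patient-specific and can be far above the one implied by 15% versus 40%.

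This rests on the inference, from the Inclusion criteria and Procedure sections, that nobody is at 0 mg at baseline; the article does not say so outright. It also rests on the flat rates after month 6 in step 2 and on a small number of simulated data sets in steps 3 and 4, which omit the GP level.

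**What to change.** State the primary analysis as one multilevel logistic regression of the 6-month binary outcome on arm, with patients nested in GPs and dropouts classified as already planned. Remove baseline as an outcome occasion. Analyse 9 and 12 months as secondary, using follow-up visits only, with arm-by-visit terms and a stated outcome variable for those visits (current status or cumulative). If a repeated-measures model is preferred, restrict it to 6, 9 and 12 months, use current status, and name the 6-month contrast as the primary test.

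A GP random intercept also gives a conditional odds ratio, but the gap is small. Taking the ICC of 0.05 on the latent scale, the variance is (π²/3)·0.05/0.95 = 0.173, and the conditional log OR exceeds the marginal one by a factor of about √(1 + 0.346·0.173) = 1.03.

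The cost is a change of wording. No new data are needed and N stays at 138, because that number already assumes this single comparison: 69·0.85 = 58.65 evaluable per arm, and 58.65/1.2 = 48.9 effective, gives about 80% power.

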### Secondary analyses

We will use Cox regression analysis for differences in time to relapse/recurrence in depression and/or anxiety and multilevel regression analysis for all other secondary outcomes. Baseline scores of all continuous variables will be included as covariates in the respective analyses.

### Cost-effectiveness evaluation

The cost-effectiveness evaluation will be carried out from both a medical and societal perspective considering direct health related costs and societal costs following the Dutch guideline [45]. Total costs, measured with the TIC-P, will be estimated using an incremental bottom-up (micro-costing) approach, where information on each element of service used is multiplied by an appropriate unit cost and summed to provide an overall total cost [46]. We will consider four types of costs: (1) intervention costs of offering the MBCT, (2) costs stemming from health care uptake related to discontinuation, (3) patients’ and their family’s out-of-pocket costs, (4) costs stemming from productivity losses due to absenteeism related to discontinuation. The recall period will be 4 weeks at baseline, and will consist of the entire period between each of the follow-up assessments. Intervention costs will include all the costs that will contribute to the development and administration of the MBCT, for example costs of training and travel expenses. Total costs for each patient will be obtained by multiplying these data with standard costs, based on the Dutch guideline for costing research [45]. Cost as outcome are mostly skewed. In our analysis we will take skewness into account by using a GLM approach with a gamma distribution and log link. Cluster effects will be accounted for by cluster robust standard errors. Descriptive statistics on costs will be presented as well. Health-related quality of life from baseline up to 12 months will be used to calculate QALYs based on the EQ-5D using the trapezium rule. Incremental cost-effectiveness will be expressed in terms of incremental costs per QALY gained. Bootstrap simulations with 1,000 replications will be used to produce uncertainty intervals in our economic evaluation, taking into account the correlations between costs and QALYs. A cost-effectiveness acceptability curve (CEAC) will be produced to show the probabilities that either of the tested strategies is the cost-effective option, given certain values for the cost-effectiveness threshold (i.e. a willingness to pay for a QALY gained). If there are baseline differences between groups a net monetary benefit and regression based framework will be used. Uncertainty surrounding non stochastic parameters (like prices) will be explored using one way sensitivity analyses.

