### Procedure

Eligible GPs will be informed about the study and requested to participate. GP’s will be randomly allocated to either SPD alone or SPD + MBCT. The GPs are asked to identify patients using antidepressant medication for more than 9 months in their electronic prescription system. Between 2016 and 2018 interested GP’s will invite their long-term-users of ADM to discuss tapering via a letter and return form. GPs are requested to inform the research team about the number of patients who will not get an invitation including the reason(s).Patients’ reply forms will be collected by the research team and interested patients will be invited to complete the online screening questionnaire which includes demographic characteristics, ADM-use, the Patient Health Questionnaire [27] and Generalized Anxiety Disorder [28]. Subsequently, they will receive an information brochure about tapering, a decision aid and an invitation to make an appointment with their GP. Patient and GP are encouraged to use the decision aid as a conversation guideline to make a shared decision on whether or not to discontinue the antidepressant medication. After having consulted their GP about tapering and if they decide to start tapering, patients will receive an invitation to participate in the RCT and an invitation for a research interview. During the interview written informed consent that has been approved by the Medical Ethics Committee of Arnhem-Nijmegen will be obtained. The psychiatric structured diagnostic interview that will be conducted [29] will take about 60–90 min altogether. Patients will also be requested to complete baseline measures online. Thereafter patients will be advised to plan meetings with the Mental Health Assistant for their SPD. Those patients allocated to SPD + MBCT will be invited to participate in the first upcoming MBCT course. Follow up measurements take place six, nine and 12 months after baseline using telephone interviews and online questionnaires. The first assessment took place in February 2017, the last assessment will take place in July 2019.

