### Outcome measures

Table 1 presents an overview of the outcome measures and the time points of assessments.

**Table 1 Tab1:** Overview of the measures and corresponding time points

Measure	Target concept	Baseline (T0)	FU6 months (T1)	FU9 months (T2)	FU12 months (T3)
Daily calendar	Use of antidepressants	Daily registration during 12 months			
SCID I modules*	Global psychopathology	*	*	*	*
DESS	Discontinuation symptoms	*	*	*	*
IDS-C	Depressive symptoms	*	*	*	*
STAI	Anxiety trait & state	*	*	*	*
M.I.N.I. plus Suicidal	Suicide cognitions	*	*	*	*
RRS-brooding	Rumination brooding	*	*	*	*
MHC-SF	Positive mental health	*	*	*	*
FFMQ-SF	Mindfulness skills	*	*	*	*
SCS-SF	Self compassion	*	*	*	*
TIC-P	Direct and indirect costs	*	*	*	*
EQ-5D	Quality of life	*	*	*	*

Note. *Scid I modules screening, mood episodes & disorders and anxiety disorders. All questionnaires are online self-reports except SCID-I modules and IDS-C (interview) and daily calendar (pen&paper). If participants do not have internet-access paper questionnaires will be offered

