#### Primary outcome measure

Our primary outcome will be full discontinuation of antidepressant medication (= 0 mg) within 6 months after starting the intervention. Use of medication will be measured with daily calendars. Patients will be invited to fill out paper calendars describing their type of antidepressant, daily milligrams used and consultations to GP or mental health assistant regarding tapering. In case of missing data in the reports, the GP will be contacted to check the GP prescription database. This latter solution is considered reliable as in the Netherlands all patients are linked to only one GP who collects all medical information for a particular patient.

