
#### Cost-effectiveness

*Resource use* such as use of care, medication and illness related to work will be measured by means of the TIC-P. The TIC-P is a self-report inventory that consists of 38 items and measures both direct costs, i.e. care consumption of people suffering from psychiatric illness, and indirect costs, i.e. costs associated with production loss over the 12 month follow up period [43].To evaluate *quality of life* the EuroQol-5D, self-report version, will be used [44]. The EQ-5D uses a descriptive system of health-related quality of life states consisting of five dimensions (mobility, self-care, usual activities, pain/discomfort and anxiety/depression) each of which can take one of three responses. In addition it contains a visual analogue scale to determine Quality Adjusted Life years (QALYs). The Dutch translation will be used.

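### Antidepressant use and tapering contacts are costed from questionnaire recall of about 6 months at the first follow-up, although the trial already keeps a 12-month daily calendar of these items

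*Protocol article*

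**What the plan says.** All references are to the protocol article.

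- **Cost source** (Cost-effectiveness evaluation): "Total costs, measured with the TIC-P, will be estimated using an incremental bottom-up (micro-costing) approach". The Cost-effectiveness subsection describes resource use "such as use of care, medication and illness related to work will be measured by means of the TIC-P".
- **Recall window** (Cost-effectiveness evaluation): "The recall period will be 4 weeks at baseline, and will consist of the entire period between each of the follow-up assessments".
- **Assessment times** (Procedure): "Follow up measurements take place six, nine and 12 months after baseline using telephone interviews and online questionnaires".
- **Calendar** (Primary outcome measure): patients complete "paper calendars describing their type of antidepressant, daily milligrams used and consultations to GP or mental health assistant regarding tapering". Table 1 gives its duration as "Daily registration during 12 months" and names no arm restriction.
- **Back-up for the calendar** (Primary outcome measure): "In case of missing data in the reports, the GP will be contacted to check the GP prescription database". The section regards this source as reliable because each Dutch patient is linked to a single GP.
- **MBCT costs** (Cost-effectiveness evaluation): a separate intervention-cost category covering development and delivery, for example training and travel. SPD has no such line, so its contacts fall under the category for care use connected with stopping the drug.

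**The concern.** The longest recall window in the study falls on the months in which patients are advised to taper and in which most meetings with the GP or mental health assistant are expected. Doses change repeatedly during a taper, which makes a summary from memory a weak basis for drug volumes. For two cost items, antidepressants and tapering consultations, the trial already holds a prospective daily record. That record is relied on for the primary outcome but is not named as a source for costs.

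The numerator of the cost per QALY is at stake. MBCT cost need not shrink with poor recall, because it is built up separately. Any true difference between arms in the recalled items can be distorted. The safeguards in the costing section do not test this: the gamma GLM deals with skewness, the bootstrap with sampling uncertainty, and the one-way sensitivity analyses with fixed quantities such as prices. None of them varies the measured volumes.

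**Working it through.** The documents give no cost or recall-accuracy figure, so there is no figure of the plan to reproduce on this point.

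**1. Recall windows.** These are inferred from the assessment times, taking the first follow-up window to start at baseline. Read literally, the recall sentence covers only intervals between follow-up assessments and would leave months 0–6 uncosted. The Cost-effectiveness subsection refers to a 12-month period, so the inferred reading is the sensible one.

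| Assessment | Window | Approx. weeks |
|---|---|---|
| Baseline | 4 weeks | 4 |
| 6 months | months 0–6 | 26 |
| 9 months | months 6–9 | 13 |
| 12 months | months 9–12 | 13 |

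The 6-month window is 26/13 = 2 times each later window and covers 6/12 = 50% of follow-up.

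**2. What falls in months 0–6.** Finishing the taper within 6 months is advice (SPD section). The MBCT course has sessions 1–4 weekly and 5–8 fortnightly, so first to last session spans 3 × 1 + 4 × 2 = 11 weeks. It ends within 26 weeks only if it starts within 26 − 11 = 15 weeks of baseline. Patients join the next available course and no maximum wait is stated. Most contact is therefore expected in this window, but not necessarily all of it.

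**3. Overlap of the two sources.**

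| Item | TIC-P | Daily calendar | Stated back-up |
|---|---|---|---|
| Antidepressants | medication, by recall | type and mg, daily | GP prescription database |
| GP or assistant contacts about tapering | within use of care, by recall | recorded | none stated |
| Other care, other drugs, productivity | by recall | not recorded | none stated |

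The calendar can replace or check only the first two rows.

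**4. Effect on the cost difference.** Let M be MBCT cost, counted in full. Let C1 and C0 be the true costs of the recalled items with SPD + MBCT and with SPD alone, and let r be the fraction recalled.

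- True difference: M + (C1 − C0)
- Observed difference, same r in both arms: M + r(C1 − C0)
- Bias: (r − 1)(C1 − C0)

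Illustration in arbitrary units, all values assumed: M = 100, C0 = 100, r from 0.9 down to 0.7.

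| C1 | True difference | Observed (r = 0.9 to 0.7) | Bias |
|---|---|---|---|
| 100 | 100 | 100 to 100 | 0 |
| 70 | 70 | 73 to 79 | +3 to +9 |
| 130 | 130 | 127 to 121 | −3 to −9 |

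If recall differs by arm, the observed difference is M + r1·C1 − r0·C0. With C1 = C0 = 100 the true difference is 100. Then r1 = 0.7 and r0 = 0.8 give 100 + 70 − 80 = 90, and r1 = 0.8 and r0 = 0.7 give 100 + 80 − 70 = 110.

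The bias can thus be zero, positive or negative.

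**The case against.** The strongest reply is that nothing here is contradictory. Whole-interval recall covers all 12 months without extrapolating from short windows. Naming the TIC-P cannot exclude every other source, since the same section costs MBCT separately. Mapping each item to a data source often belongs in a health-economic plan that is not shown. This stands in part: the protocol makes no misstatement, and the point is an improvement to a stated choice. The section does, however, fix the instrument and its recall windows, and the calendar is not named among the cost sources.

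A second reply concerns the remedy. A 26-week TIC-P total cannot fill single missing calendar days. The documents do not show that the TIC-P separates tapering visits from other GP visits. The stated back-up covers prescriptions, not consultations. Patients know their arm, so paper-calendar gaps could differ between arms. All of this stands, and it is why the contacts belong in a sensitivity analysis only.

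A reader might infer that under-recall understates the cost difference on one side only, because MBCT cost is protected from recall. The documents do not support that. Both arms receive SPD and complete the same TIC-P at the same times, so both are exposed. The protocol describes one SPD package and tries to keep the assistant blind, so it predicts no difference in contacts. The expected discontinuation rates of 15% and 40% suggest that drug use will differ, but they give no costs and no recall accuracy. Nor can a percentage error be quoted, because any such figure follows from the values chosen for r and C1 − C0. The shorter 4-week baseline window adds no separate problem: re-expressing baseline cost per week only rescales a covariate and leaves the treatment estimate in a linear net-benefit regression unchanged.

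**Conclusion.** The point holds as a cheap improvement to a secondary, economic analysis. Antidepressant use and tapering contacts are costed from recall of about 6 months at the first follow-up, while a daily record of the same items exists and is trusted for the primary outcome. Any true between-arm difference in these items is measured with a bias of (r − 1)(C1 − C0) if recall is equal in both arms. Its size and direction cannot be derived from the documents, and it may be zero.

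The conclusion rests on two readings: that the first follow-up window runs from baseline to 6 months, and that MBCT cost is built up from delivery records and not from patient recall. Both fit the text, though neither is stated in so many words.

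**What to change.** In Cost-effectiveness evaluation:

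1. Take antidepressant volumes from the daily calendar, with the GP prescription database for gaps, and drop antidepressants from the TIC-P total so that they are not counted twice.
2. Keep the TIC-P for all other care and for productivity.
3. Add a sensitivity analysis that replaces TIC-P volumes of GP and mental health assistant contacts about tapering with calendar counts, where the TIC-P items allow this without double counting.
4. Report calendar completeness by arm.

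The cost is analysis-plan wording and data handling. No new data are needed for the calendar counts, and the prescription check is already planned for the primary outcome. The recall windows can hardly be changed now, with the last assessment set for July 2019, but the source used in the analysis can. The small downside is that paper calendars have gaps, which may differ by arm; step 4 makes that visible.

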### Sample size

Based upon earlier research we expect a discontinuation rate for patients in the SPD condition of 15% and a 40% discontinuation rate for patients in the SPD + MBCT condition. We used data from Eveleigh [17] to predict discontinuation in the SPD condition (where 6% successful discontinuation was observed according to very strict criteria, and we made adaptations to align with the context of the current setting, e.g. all patients had a clear intention to taper). To estimate the rate in the SPD + MBCT condition, we looked at studies with available data on adherence to tapering after MBCT, ranging between 53 and 71% [23–25]. Again we made a conservative adaptation of 40% to account for differences in time frame (6 versus 15 months), intention-to-treat versus per-protocol sample, and considering the difficulties in discontinuation and withdrawal symptoms as mentioned in the literature [16]. The following assumptions were used in the sample size calculation: power 80%, alpha of 5% and two tailed testing. Due to the fact that the trial will be cluster randomized, the calculated number of patients assuming individual randomization, has to be inflated by a design factor. To account for this an intra-class correlation (ICC) of 0.05 was used, which is commonly used for research including outcome measures [26]. With regard to the mentioned research we also assume a dropout rate of 15%. Taking these figures into account a total of 24 GPs have to be included, with 138 patients participating in the study; including 69 patients per described condition; presenting an estimate of 5 participating patients per GP.

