#### Mindfulness based cognitive therapy (MBCT)

MBCT will be offered according to the treatment protocol developed for recurrent depression [30], adapted to the specific needs of patients discontinuing their antidepressant medication. The psycho-education sections about depression will be extended with information about pro and cons of stopping antidepressants, withdrawal effects and anticipatory anxiety. Based on our expectation that the discontinuation process may take longer than is currently regarded as common practice, sessions 1–4 will take place on a weekly and sessions 5–8 on a fortnightly basis. Each session will last 2.5 h with a 6-h silent day between session six and seven. In addition to the group sessions, participants will be instructed to practice mindfulness for approximately 30 min a day. Participants will receive a digital link to download guided meditations and yoga exercises for home practice. The mindfulness courses will be provided by teachers qualifying the advanced criteria of the Association of Mindfulness Based Teachers in the Netherlands and Flanders, which include a) relevant professional training; b) having attended MBSR / MBCT as a participant; c) a minimum of 150 h of education in MBSR/MBCT background and theory, training in teaching formal and informal meditation practices, psycho-education and inquiry, supervision and teaching an MBSR or MBCT course including a reflection report; d) teaching a minimum of two courses per 2 year; e) minimum of 3 years of practicing meditation regularly and attending retreats; and f) continued training. All teachers will receive additional training in using the specific study protocol at the start of the project. We will organize two peer supervision meeting per course during the intervention phase of the trial. Teaching sessions will be videotaped to check treatment integrity. A random selection of two tapes per teacher will be rated for treatment adherence and competency by highly experienced MBCT/MBSR teachers with the Mindfulness-Based Cognitive Therapy Adherence Scale [31].

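### Base-case intervention costs include the development of MBCT although the cost type is the cost of offering it, so a one-off cost is charged to the SPD + MBCT arm only

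*Protocol article*

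**What the plan says.** All of the costing text is in the protocol article, Cost-effectiveness evaluation.

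- The cost types: "We will consider four types of costs: (1) intervention costs of offering the MBCT", followed by discontinuation-related health care, out-of-pocket costs and productivity losses.
- The content of the first type: "Intervention costs will include all the costs that will contribute to the development and administration of the MBCT". Training and travel are given as the examples.
- The costing method is bottom-up: "information on each element of service used is multiplied by an appropriate unit cost and summed to provide an overall total cost".
- The step to the patient level: "Total costs for each patient will be obtained by multiplying these data with standard costs", with unit prices from the Dutch costing guideline.
- The outputs are incremental cost per QALY, bootstrap uncertainty intervals and a cost-effectiveness acceptability curve (CEAC). One-way sensitivity analyses are planned for non-stochastic parameters, with prices as the only example.

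The section on MBCT says that an existing treatment protocol is adapted for patients who are discontinuing, with extended psycho-education. It adds: "All teachers will receive additional training in using the specific study protocol at the start of the project".

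**The concern.** The label and the content rule describe two different quantities. The cost of offering MBCT recurs with each course. The cost of developing it is spent once, and a practice or insurer deciding whether to offer the course later does not pay it again. The content rule puts both into the same cost type and, by covering all such costs, leaves no room to set development aside.

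The comparison is SPD + MBCT against SPD alone, so nothing in the control arm offsets the addition. If the same amount is added for every patient in one arm, the bootstrap and the cluster-robust standard errors will not show it, because it shifts the mean without changing the spread. The results at stake are the declared economic ones: incremental cost, cost per QALY and the CEAC. If development cost is material, they would answer what the project spent rather than whether adding MBCT to SPD is worth its cost.

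**Working it through.** **1. The statements side by side.** Type 1 is the cost of offering MBCT. The bottom-up method counts elements of service used. The content rule counts development as well as administration. Development is neither an element of service that a patient uses nor a cost of running another course. By contrast, the group sessions (8 x 2.5 h + 6 h = 26 contact hours per course, from the MBCT section) recur each time and fit both the label and the method.

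**2. Direction of the effect.** Let ΔC be the incremental cost per patient without development, ΔQ the QALY difference, λ the willingness to pay, and c > 0 the development cost per patient charged to the SPD + MBCT arm.

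- Net monetary benefit: λΔQ − ΔC becomes λΔQ − ΔC − c. It falls by c at every λ, whatever the sign of ΔQ.
- CEAC: the proportion of bootstrap replicates with λΔQ − ΔC > 0 becomes the proportion with λΔQ − ΔC > c. It cannot rise at any λ and will generally fall.
- Cost per QALY: ΔC/ΔQ becomes ΔC/ΔQ + c/ΔQ. It rises only if ΔQ > 0.

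**3. The arm size used for illustration.** The Sample size section gives "including 69 patients per described condition". From its inputs (15% against 40%, two-sided 5%, power 80%, no continuity correction) n = 49 per arm. The design effect is 1 + (5 − 1) x 0.05 = 1.2, so 49 x 1.2 = 58.8, and 58.8 / 0.85 = 69.2. The stated 69 reproduces.

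**4. Size under assumptions.** The article gives no development cost, unit cost or QALY difference. Let D be an assumed one-off sum in euros and n the number of patients it is spread over, so c = D/n. The last column assumes ΔQ = 0.02.

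| D (assumed) | c at n = 69 | c at n = 690 | Added cost per QALY at n = 69 |
|---|---|---|---|
| 5,000 | 72 | 7 | 3,623 |
| 10,000 | 145 | 14 | 7,246 |
| 20,000 | 290 | 29 | 14,493 |
| 50,000 | 725 | 72 | 36,232 |

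For D = 20,000 and n = 69, the added cost per QALY is 28,986 at ΔQ = 0.01 and 5,797 at ΔQ = 0.05. The result therefore depends heavily on three quantities that the article does not give: D, n and ΔQ.

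**The case against.** The strongest case on the other side has four parts.

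- *The article does not say that the sum is divided over trial patients.* A unit cost for a course could already spread set-up over expected routine use, and an article may leave such detail to a fuller document. This stands. A reader might infer that the cost per QALY depends on how many patients the trial recruits, but that follows only if the trial arm is the denominator, which the text does not state.
- *Development is undefined and may be meant loosely.* The examples given are training and travel, and an existing protocol is only adapted. This stands as a limit on size: true one-off development may be small. It does not remove the conflict, because two analysts following the text could build different base cases.
- *The label is only shorthand, and the later sentence defines it.* This is possible. But development also sits badly with a method that prices elements of service used, so the mismatch is not with the label alone.
- *A societal perspective counts all costs, and including development is conservative against MBCT.* Perspective decides whose costs count. It does not turn a one-off cost into part of the cost of offering the course. A conservative variant belongs in a sensitivity analysis, where it can be seen for what it is.

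The planned one-way analyses could hold such a run, but none with and without development cost is named.

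**Conclusion.** The point holds as a conflict within the stated costing rule. Followed as written, the rule adds a one-off cost to the SPD + MBCT arm alone. That lowers its net monetary benefit at every willingness to pay, and it raises the cost per QALY if the QALY gain is positive.

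A reader might go further and conclude that the cost per QALY is overstated by a known or large amount. The documents do not support that. They give no cost or QALY figures, do not define development and state no denominator, so the euro amounts in the table show only the range under assumptions. Calling the result overstated also presumes that the decision concerns routine delivery, where development is already paid for.

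The point affects the economic evaluation only. The primary outcome, the sample size and the clinical analyses are untouched. It should be corrected, because the correction is cheap and these are the declared economic outputs.

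**What to change.** In Cost-effectiveness evaluation, replace the sentence on the content of intervention costs with wording such as:

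> Base-case intervention costs are the recurring costs of delivering MBCT: teacher contact and preparation time, supervision, materials, room and travel. Teacher training, including the training at project start, is spread over the number of courses a teacher is expected to give. One-off development costs and research-only costs, such as the rating of videotaped sessions, are excluded. A one-way sensitivity analysis adds development cost and states the number of patients or courses over which it is spread.

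The last item fits within the one-way analyses already planned. The cost is a wording change and one further run, with no new data. The small downside is that the base case no longer shows everything the project spent on MBCT; the sensitivity analysis reports the development part.
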